### Variables

#### Demographics

Age, sex, underlying pathology and the type of surgery will be collected.

#### Outcome measures

POA assessment: All subjects included in the study will be filmed at four moments to later evaluate their POA by the m-YPAS scale.Saliva and blood cortisol determination: Patients’ saliva will be collected by Salivette® device at time-points M1 and M2. Likewise, a 5-ml blood sample will be obtained at time-point M3 to determine blood cortisol levels after the induction of anaesthesia.Induction Compliance Checklist: It will be performed by the anaesthesiologists in the operating room.Assessment of anaesthetic recovery with or without presence of delirium using PAEDS (PediatricAnesthesia Emergence Delirium Scale) [21] and assessment of post-anaesthetic recovery in PACU using Aldrete [22].Vital signs on arrival at PACU and every 30 min until the transfer to general ward: heart rate and respiratory rate.Pain Scales: Multidimensional pain scale for children under 3 years old, face pain scale for children aged 4–7 years and Visual analog scale for children older than 7 years old.Need of postoperative analgesia.Time to hospital discharge after leaving the operating room, in minutes.Evaluation on perceived healthcare quality: to fulfil this objective, a self-administered satisfaction survey will be completed by patients and parents/legal guardians after anaesthesia recovery and once hospital discharge is indicated. Healthcare professionals that usually attend children submitted to Major Outpatient Paediatric Surgery and that are involved in the study will complete the survey when the study is finished. The survey used is elaborated following the general criteria established by the Madrid Health Service for the elaboration of citizen satisfaction surveys [23]. Paediatric patients under 5 years old or older patients and parents/legal guardians with cognitive impairment or difficulty in understanding the language, will be excluded from this evaluation.

### Statistical analysis

#### Sample size

Anxiety in children will be evaluated through comparing m-YPAS score between the moment of induction of anaesthesia and the presurgical moment prior to the entrance to the operating room. The sample size calculated will allow detection of a difference of means of 14.3 points at m-YPAS between the group with parental accompaniment and hydroxyzine (mean: 18; standard deviation (SD): 13.5 points) compared to the group with parental accompaniment only (mean: 32.3; SD: 24.2 points) [4, 24]. With a sample size of 47 subjects in each group, we would have a power of 90%, with a level of significance of 0.025, to detect these differences. The final sample size would be 188 subjects (47 in each group).

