### Treatment guideline

On the day of surgery, once the IC and, if applicable, child agreements have been signed and the selection criteria have been confirmed, the non-blinded nurse will randomise the subjects. Juice, with or without hydroxyzine, will be administered to subjects at least 30 min prior to the subject being transferred to the surgical ward.

POA evaluation will be performed at the following time-points:
Time-point 0 (M0): Considered the baseline status because it is the moment when the patient arrives to the pre-surgical hospitalisation area prior to being in contact with any method to reduce POA. At this time-point, the investigators will record a film in order to evaluate the patient’s baseline state of anxiety by the m-YPAS.Time-point 1 (M1): During the stay in the pre-surgical hospitalisation area, at least 30 min after receiving the assigned strategy. At this moment, investigators will record a film to later evaluate the subject’s preoperative state of anxiety by the m-YPAS. The first Salivette® will be provided to the patient for the collection and determination of salivary cortisol. Salivette® will be collected before leaving the pre-surgical hospitalisation area.Time-point 2 (M2): Moment when the patient is transferred to the operating room up to the entrance to the surgical ward and parental separation. The investigators will record a film during the transfer to the operating room and up to the entrance to the surgical block to later evaluate a subject’s preoperative anxiety by the m-YPAS scale. At this time-point, the second Salivette® will be collected when the patient is placed in the operating room bed.Time-point 3 (M3): During the induction of anaesthesia in the operating room: The investigators will record a film during the induction of anaesthesia to later evaluate subject’s preoperative anxiety by the m-YPAS scale. At this time-point, the anaesthesiologist will complete the Induction Compliance Checklist and a blood sample (5 ml) will be obtained for cortisol analysis.Stay in Post-Anaesthetic Care Unit (PACU): Upon arrival at PACU and until recovery from anaesthesia, the variables about recovery from anaesthesia, pain, delirium, vital signs and postoperative analgesia will be collected.Stay in General Ward: at the time of hospital discharge, parents/legal guardians will complete satisfaction survey as will children aged 5 years or older. Healthcare professionals will complete this survey at the end of the study.

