#### Data analysis

The analysis will be performed by protocol and intention to treat. The qualitative variables will be presented with their frequency distribution. The quantitative variables will be summarised with their mean and SD. The quantitative variables that show an asymmetric distribution will be summarised with the median and interquartile range.

Comparison of the baseline characteristics of the four study groups will be performed. The association between qualitative variables will be evaluated by Pearson’s χ^2^ test or by Fisher’s exact test. For quantitative variables, means will be compared with Student’s *t* test for independent groups or with nonparametric test for the quantitative variables if they do not fit a normal distribution.

For the main outcome (POA) and secondary quantitative variables evaluated, a repeated measures analysis of the variance (ANOVA) will be carried out. The Bonferroni correction method will be used for multiple comparisons.

A comparison of means in each time-point and of the interaction between the dependent variable of the analysis (test score) and the study group (inter-subject factor) will be assessed. If any baseline characteristics between groups present clinically relevant differences, the model will be adjusted by those variables. Qualitative variables will be compared between groups using Pearson’s χ^2^ test. The relative risk with 95% confidence intervals will be calculated. If any of the baseline characteristics between groups presents statistically significant and/or clinically relevant differences between the four study groups, odds ratio (ORs) will be estimated using a logistic regression model. For all tests, a significance level of 5% will be accepted. The analysis of the data will be done by the statistical package STATA 12.0.

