## Discussion

POA is observed amongst children during their stay in the operative room with a prevalence of 83.3% [23]. Adverse psychological and behavioural changes (decrease in children’s self-esteem and emotional well-being, increased anxiety, sleep disturbances and social isolation) have been observed in a rate of 25% in children during hospital stay and even at 1-year post-discharge [6]. A recent systematic review also identified negative psychological sequelae in children [18].

The search for an ideal premedication drug to reduce POA in children is ongoing. The drugs used as anxiolytics are not exempt of side effects and the studies about this issue are limited to dental procedures [14–16]. One study [15] evaluated hydroxyzine at doses of 0.15 mg/kg, yet the dose proposed in our clinical trial is of 2 mg/kg.

The role of clowns and hydroxyzine in the management of anxiety is controversial as there are studies both for and against them [18–20]. We have not found any study that determines the additive effect on anxiolysis of distracting techniques with clowns and pharmacological treatment, as we propose in our case.

The proposed study has some limitations. The clowns are not always at the hospital; therefore, assignment to this intervention depends on whether they are present or not on the day of surgery. In order to reduce this bias, the healthcare professionals that plan the patient’s surgery will not know when the clowns come to the hospital.

The main objective of this study is the evaluation of POA. Studies that evaluate POA are difficult to perform and interpret, mostly because of the difficulty in assessing anxiety attributable to the surgical act. According to some studies [3, 25], the moment with the maximum rate of anxiety and fear associated with the entire surgical procedure is during anaesthetic induction. Therefore, evaluating the child’s anxiety during anaesthetic induction is very useful to determine whether the strategies used in the presurgical period have been effective in reducing anxiety [26]. That is the reason why in the present study, POA is evaluated in both moments. Most studies on this topic use a presurgical anxiety rating scale, the m-YPAS [23, 24, 26, 27].

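### The anxiety comparison behind the sample size sets induction against a moment that is naturally post-treatment; read as a change score, it subtracts any effect already achieved before theatre

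*Protocol article*

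**What the plan says.** The Sample size section of the protocol article states that anxiety will be evaluated by "comparing m-YPAS score between the moment of induction of anaesthesia and the presurgical moment prior to the entrance to the operating room". It does not label the presurgical moment. It then sizes the trial on a 14.3-point difference between hydroxyzine (mean 18, SD 13.5) and parental accompaniment only (mean 32.3, SD 24.2), without saying whether these are scores at one moment or changes between two.

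The Treatment guideline section defines four filmed moments:

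- M0, the baseline on arrival, "prior to being in contact with any method to reduce POA".
- M1: "During the stay in the pre-surgical hospitalisation area, at least 30 min after receiving the assigned strategy".
- M2: "Moment when the patient is transferred to the operating room up to the entrance to the surgical ward and parental separation".
- M3: during induction of anaesthesia.

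The juice, with or without hydroxyzine, "will be administered to subjects at least 30 min prior to the subject being transferred to the surgical ward".

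In the Data analysis section, for the main outcome, "a repeated measures analysis of the variance (ANOVA) will be carried out", with means compared at each time-point and an interaction with study group. Baseline variables enter the model only where the groups differ to a clinically relevant degree. The Discussion says that "the moment with the maximum rate of anxiety and fear associated with the entire surgical procedure is during anaesthetic induction", argues that anxiety at induction shows whether the presurgical strategies worked, and adds that anxiety is evaluated at both moments.

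**The concern.** A change score measures a treatment effect cleanly only if its reference value was taken before treatment. Here the reference moment appears to be one at which the strategies should already be working. Subtracting it removes the benefit the trial is looking for.

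The Background makes this more than theoretical. It reports that humour and laughter seem to lower anxiety in the ward area before theatre, while a benefit inside the surgical area has not been shown. With that pattern, clown groups would start lower and rise more by induction, so a change from M1 or M2 would make a helpful strategy look harmful. The Discussion's rationale calls instead for the difference between groups at induction, which this change does not estimate.

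**Working it through.** **1. The plan's own figure.** Inputs from the Sample size section: difference 14.3; SDs 13.5 and 24.2; level 0.025; power 90%.

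- Pooled SD = √((13.5² + 24.2²)/2) = √383.9 = 19.59.
- n per group = 2 × (2.241 + 1.282)² × 383.9 / 14.3² = 46.6, rounded up to 47.
- SE at n = 47 is √((13.5² + 24.2²)/47) = 4.042. Power = Φ(14.3/4.042 − 2.241) = 90.3%.

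The stated 47 is reproduced with a two-sided level of 0.025. A one-sided 0.025 would give 40.

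**2. Which moment is the comparator?** M2 covers the transfer up to the surgical entrance and is the closest match. M1, in the ward area, is the next. M1 is filmed "at least 30 min after receiving the assigned strategy", and the juice precedes the transfer by at least 30 min, so both are post-treatment. M0 is the only pre-treatment film, and it is tied to arrival, not to entry to theatre.

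**3. What a change would estimate.** Let D3 be the reduction in m-YPAS due to treatment at induction, and Dpre the reduction at the presurgical moment. The between-group difference in change, expressed as benefit, is D3 − Dpre. Using the plan's 14.3 points as an illustrative effect:

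| Pattern | Dpre | D3 | D3 − Dpre |
|---|---|---|---|
| Effect only at induction | 0 | 14.3 | 14.3 |
| Half present before theatre | 7.15 | 14.3 | 7.15 |
| Sustained | 14.3 | 14.3 | 0 |
| Only before theatre | 14.3 | 0 | −14.3 |

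The difference at M3 alone is D3 in every row. If the reference were M0, no treatment effect could exist there and the change would also estimate D3 for the randomised factor.

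**4. What M0 as covariate would give.** Error variance is multiplied by 1 − ρ², where ρ is the M0–M3 correlation. The document gives no correlation, so ρ is an assumption. The last two columns also assume that 14.3 and the SDs describe induction scores.

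| ρ | Variance factor | n per group for 90% | Power at 47 |
|---|---|---|---|
| 0.3 | 0.91 | 46.6 × 0.91 = 42.4, so 43 | Φ(3.538/√0.91 − 2.241) = 92.9% |
| 0.5 | 0.75 | 46.6 × 0.75 = 35.0, so 35 | Φ(3.538/√0.75 − 2.241) = 96.7% |
| 0.6 | 0.64 | 46.6 × 0.64 = 29.8, so 30 | Φ(3.538/√0.64 − 2.241) = 98.5% |

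Here 3.538 = 14.3/4.042.

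**The case against.** The strongest reply is that the document never uses the word change for this outcome. Comparing two moments, together with the Discussion's remark that both are evaluated, fits two separate assessments. The Data analysis section already compares means at each time-point, and that includes M3. The article also condenses a fuller protocol. This stands to the extent that the subtraction is conditional on the reading. It does not remove the point: the Sample size section positively states the comparison, the two readings answer different questions, and neither section chooses between them or names M3 as the primary contrast.

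It can also be said that an unadjusted M3 comparison is valid for the randomised hydroxyzine factor and that M0 adjustment is a matter of efficiency. That is fair for hydroxyzine. Clown accompaniment, however, depends on availability on the day of surgery, so baseline anxiety may differ there by more than chance. Deciding on adjustment after seeing the groups is a weaker rule than fixing it in advance.

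A reader might infer two stronger points that the documents do not support:

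- **That the repeated-measures ANOVA dilutes the effect by counting M0 as an outcome.** A group effect averaged over four moments would fall to 14.3 × 3/4 = 10.7 points, but the Data analysis section names no such average and does not list the moments entered. Its comparisons at each time-point are undiluted, and including M0 helps the group-by-time interaction to detect a sustained effect.
- **That power collapses.** Putting 7.15 points into the plan's power formula takes the outcome as a change but takes 14.3 and its SDs as induction scores. Read consistently either way, the planned power is 90%. A change score would also need its own SD, which depends on a correlation that is not given.

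**Conclusion.** The point holds in conditional form. The comparison that the Sample size section describes uses a presurgical moment that, on its natural reading, is post-treatment. If it is analysed as a change, a sustained effect scores zero and an effect confined to the time before theatre changes sign. This rests on two assumptions: that the unlabelled moment is M1 or M2, and that the comparison is a change. The text allows both and confirms neither. The sample size arithmetic is correct, and no loss of power can be quantified from the document. The gain from fixing M0 as a covariate is about 9% to 36% of error variance for an assumed correlation of 0.3 to 0.6.

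**What to change.** In the Sample size and Data analysis sections:

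- Name the between-group difference in m-YPAS at M3 as the primary contrast, with M0 m-YPAS as a prespecified covariate. Either an ANCOVA or a mixed model over M1–M3 with M0 as covariate and a group-by-time term would do.
- Make M1 and M2 secondary, analysed in the same way.
- State whether 18, 32.3 and 14.3 are induction scores or changes. If they are changes, say from which moment, and re-derive the sample size for the M3 contrast.

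The cost is wording only. All four films are already planned, and if the figures are induction scores, 47 per group remains sufficient. The change should be made before the groups are compared.

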#### Data analysis

The analysis will be performed by protocol and intention to treat. The qualitative variables will be presented with their frequency distribution. The quantitative variables will be summarised with their mean and SD. The quantitative variables that show an asymmetric distribution will be summarised with the median and interquartile range.

Comparison of the baseline characteristics of the four study groups will be performed. The association between qualitative variables will be evaluated by Pearson’s χ^2^ test or by Fisher’s exact test. For quantitative variables, means will be compared with Student’s *t* test for independent groups or with nonparametric test for the quantitative variables if they do not fit a normal distribution.

For the main outcome (POA) and secondary quantitative variables evaluated, a repeated measures analysis of the variance (ANOVA) will be carried out. The Bonferroni correction method will be used for multiple comparisons.

A comparison of means in each time-point and of the interaction between the dependent variable of the analysis (test score) and the study group (inter-subject factor) will be assessed. If any baseline characteristics between groups present clinically relevant differences, the model will be adjusted by those variables. Qualitative variables will be compared between groups using Pearson’s χ^2^ test. The relative risk with 95% confidence intervals will be calculated. If any of the baseline characteristics between groups presents statistically significant and/or clinically relevant differences between the four study groups, odds ratio (ORs) will be estimated using a logistic regression model. For all tests, a significance level of 5% will be accepted. The analysis of the data will be done by the statistical package STATA 12.0.

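### The main model, a repeated measures ANOVA over four films, would drop any child missing one film if fitted complete-case; a mixed model on all scored films, with intention to treat named primary, is a cheap improvement

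*Protocol article*

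**What the plan says.** The Data analysis section of the protocol article names the model for the main outcome: "For the main outcome (POA) and secondary quantitative variables evaluated, a repeated measures analysis of the variance (ANOVA) will be carried out". It adds a Bonferroni correction, a comparison of means at each time-point and an interaction with study group. On analysis sets it says: "The analysis will be performed by protocol and intention to treat". It does not rank the two.

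Outcome measures gives the number of repeated scores: "All subjects included in the study will be filmed at four moments to later evaluate their POA by the m-YPAS scale". Treatment guideline places the four films at arrival (M0), in the pre-surgical area (M1), during transfer (M2) and at induction (M3), and says that the investigators record them.

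The Sample size section describes its comparison as "comparing m-YPAS score between the moment of induction of anaesthesia and the presurgical moment prior to the entrance to the operating room". It targets a 14.3-point difference and sets 47 per group, 188 in all, for 90% power at a significance level of 0.025.

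The article does not say how a missing film is handled, what loss is expected, or in what form the ANOVA will be fitted.

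**The concern.** A repeated measures ANOVA can be fitted with one row per child, so that only children with all four scores contribute. In that form, a child with a good induction film but an unusable transfer film leaves the model entirely. Induction is the moment that the Discussion describes as carrying the most anxiety, and the sample size rests on a comparison involving it. Losing a valid induction score because a different film failed would waste the most informative observation.

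Two features of the plan make this worth settling. The sample size has no allowance for loss, so each child dropped takes power below the stated figure. And because neither analysis set is primary, the article gives no rule for which result counts if the two disagree. At stake are some precision and an unambiguous main result.

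**Working it through.** **Inputs from the Sample size section.** Difference 32.3 − 18 = 14.3 points; SDs 13.5 and 24.2; significance level 0.025; power 90%; 47 per group.

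**Input that is assumed.** The rate of missing films, p, is not in the documents. It is taken as 1%, 2%, 5% and 10% per film, equal in all groups and independent across films.

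**Step 1: reproduce the plan's figure.** With the normal approximation and a two-sided level of 0.025:

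n = (13.5² + 24.2²)(2.241 + 1.282)² / 14.3², with 13.5² + 24.2² = 767.89. This gives n = 46.6, so 47 per group.

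Power at n per group = Φ(14.3 / √(767.89/n) − 2.241). At n = 47 this is 90.3%. The plan's figure is reproduced. (A one-sided 0.025 would give 40 per group, so the two-sided reading is the one that fits.) Since 4 × 47 = 188, nothing was added for loss; 46 per group already gives 89.6%.

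**Step 2: complete-case over four films.** The share of children with all four films is (1 − p)⁴, which leaves 47(1 − p)⁴ per group.

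**Step 3: every available induction score.** A simple comparison at induction keeps 47(1 − p) per group, whatever happens to the other films.

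| Assumed loss per film | Children lacking at least one film | Complete children per group | Power, complete-case | Induction scores per group | Power, all induction scores |
|---|---|---|---|---|---|
| 1% | 3.9% | 45.1 | 89.0% | 46.5 | about 90% |
| 2% | 7.8% | 43.4 | 87.6% | 46.1 | 89.6% |
| 5% | 18.5% | 38.3 | 82.9% | 44.7 | 88.6% |
| 10% | 34.4% | 30.8 | 73.4% | 42.3 | 86.8% |

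**Step 4: vary the assumptions.**
- If only the two films in the sample-size contrast were required, 47(1 − p)² per group remain. Power is 86.9% at 5% loss (42.4 per group) and 82.7% at 10% (38.1 per group).
- If losses cluster completely, so that the same children lose every film, 5% loss leaves 44.65 per group (88.6%) and 10% leaves 42.3 (86.8%). These equal the last column of the table, so the gain from keeping partial records is then nil.

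**Limits of the calculation.** The 90% belongs to a two-group contrast based on two moments, not to a four-group, four-moment ANOVA. The complete-case figures are therefore approximations. The last column applies the same difference and SDs to a simple induction comparison, which is not quite the same contrast. The two power columns show the scale of the difference and are not an exact before-and-after.

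**The case against.** The strongest reply is that the article never says the ANOVA is complete-case. Fitted with one row per child per moment, it can keep a child's available films. This stands, and it makes the whole point conditional.

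Next, rules for missing films and the ranking of analysis sets are often left to the full protocol or the SAP, neither of which is shown. This also stands: their absence from an article is not an error. What remains is that the article does fix the model, and a better-suited one is available at almost no cost.

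Third, the Data analysis section also plans comparisons at each time-point. A child with only an induction score could contribute there, so such a child need not be lost from every analysis.

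Fourth, the loss rate is assumed. All four films are made in hospital between arrival and induction, with no later follow-up, so losses may be few. At 1% per film the effect on power is about one point.

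A reader might also infer that distressed children lose more films, so that less effective strategies look calmer. The documents do not support that: they say nothing about why films would be lost or whether losses differ by group.

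**Conclusion.** The point holds as a conditional, inexpensive improvement. If the ANOVA is fitted complete-case, four-film deletion costs approximate power of about 1 point at 1% loss per film and about 17 points at 10%, measured from 90.3%. Using all induction scores limits the cost to less than 1 point and about 3.5 points respectively. These sizes assume independent losses at equal rates in all groups; with fully clustered losses the two approaches coincide.

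Two stronger readings are not supported. A reader might infer that the plan contradicts its own intention-to-treat statement. Naming a repeated measures ANOVA beside intention to treat is not a contradiction, because the handling of missing scores is simply not stated. A reader might also infer that the trial is underpowered. The 47 per group is correct on the plan's own inputs, and no shortfall can be shown without a loss rate. The rule in the Blinding section that withdraws children when a clown appears on film is a separate matter and is not part of this point.

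**What to change.** In the Data analysis section, replace the repeated measures ANOVA for the main outcome with a linear mixed model for repeated measures. It should have terms for group, moment and group-by-moment, an unstructured covariance within child, and use every scored film from all randomised children. State that a missing film at one moment does not remove the child's other scores. Name the intention-to-treat analysis as primary and the per-protocol analysis as supportive.

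The downside is that the model relies on films being missing at random. Check this with one sensitivity analysis that imputes missing induction scores as worse than observed, by an amount fixed in advance.

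The cost is a change of wording. Data collection does not change, the group-by-moment comparison is kept, and the model can be fitted in the stated software.

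### The sample size assumes SDs of 13.5 and 24.2, but the main analysis is an ANOVA that ordinarily pools one error variance; some pairwise group tests may be miscalibrated

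*Protocol article*

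**What the plan says.** Under Sample size, the Protocol article looks for a difference of 14.3 m-YPAS points. The contrast is drawn "between the group with parental accompaniment and hydroxyzine (mean: 18; standard deviation (SD): 13.5 points) compared to the group with parental accompaniment only". For the second of these groups the planning values are "mean: 32.3; SD: 24.2 points". With 47 children per group, it states, "we would have a power of 90%, with a level of significance of 0.025". No SD is given for the clown-only group or for the group receiving both interventions.

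Under Data analysis, for the main outcome and the secondary quantitative variables, "a repeated measures analysis of the variance (ANOVA) will be carried out". Study group is the between-subject factor, means are compared at each time-point, and Bonferroni is named for multiple comparisons. The number of comparisons and the error term for the pairwise tests are not stated. The only distributional fallback is a nonparametric test for non-normal variables, and it stands in the paragraph on baseline characteristics. Nothing in the section provides for variances that differ between groups.

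**The concern.** The planning figures say that children given hydroxyzine vary much less than children with parents only. An ANOVA with a single error term averages the two variances. Equal group sizes protect a contrast between one high-variance and one low-variance group, because the average is then the right quantity. They do not protect a contrast between two high-variance groups or two low-variance groups.

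If hydroxyzine is what lowers the variance, clown versus control and combination versus hydroxyzine are contrasts of exactly that kind. The Background names an additive effect of the two interventions as the main objective, and the abstract asks which of the four options reduces anxiety most. At stake are a false claim for clowns alone and a missed gain from adding clowns to hydroxyzine.

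**Working it through.** **Inputs from Sample size.** SD 13.5 (hydroxyzine), SD 24.2 (parents only), difference 14.3, alpha 0.025, power 90%, 47 per group.

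**The plan's own figure.** n = (z₀.₉₈₇₅ + z₀.₉₀)² × (13.5² + 24.2²) / 14.3² = (2.241 + 1.282)² × (182.25 + 585.64) / 204.49 = 46.6, so 47. The stated size reproduces with alpha 0.025 two-sided. One-sided 0.025 or two-sided 0.05 would give 40.

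**Spread.** 24.2 / 13.5 = 1.79; variance ratio 585.64 / 182.25 = 3.2.

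**Base case.** This rests on two assumptions that are not in the documents: the clown-only SD is 24.2 and the combination SD is 13.5, and the pairwise tests use the pooled error term. Each child contributes one value.

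- Pooled SD = √[(2 × 182.25 + 2 × 585.64) / 4] = 19.59
- Pooled SE of any pairwise difference = 19.59 × √(2/47) = 4.04
- True SE, clown v control = 24.2 × √(2/47) = 4.99; ratio 4.04 / 4.99 = 0.81
- True SE, combination v hydroxyzine = 13.5 × √(2/47) = 2.78; ratio 1.45
- True SE, hydroxyzine v control = √[(182.25 + 585.64) / 47] = 4.04; ratio 1.00

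Actual size of a nominal 5% test = 2 × [1 − Φ(1.96 × ratio)]. This gives 11.3% for clown v control and 0.4% for combination v hydroxyzine. Simulation of 40,000 trials gave 11.2% and 0.5%. If Bonferroni covers six pairs (nominal 0.83%), the simulated size for clown v control was 3.4%.

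**Power, for illustration.** Take a 9-point gain of combination over hydroxyzine (assumed, not in the documents) at the 5% level. With separate variances, power = Φ(9/2.785 − 1.96) = 90%. With the pooled error, power = Φ[(9 − 1.96 × 4.042) / 2.785] = 65%.

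**Other SDs.** With equal groups and variances V, the squared ratio for clown v control is ½[1 + (V_hyd + V_comb) / (V_control + V_clown)]. For combination v hydroxyzine the inner fraction is inverted.

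| SD clown / SD combination | Ratio, clown v control | Size at 5% | Ratio, combination v hydroxyzine | Size at 5% |
|---|---|---|---|---|
| 24.2 / 13.5 | 0.81 | 11.3% | 1.45 | 0.4% |
| 18 / 13.5 | 0.84 | 10.1% | 1.32 | 1.0% |
| 13.5 / 13.5 | 0.86 | 9.2% | 1.25 | 1.5% |
| 24.2 / 24.2 | 0.91 | 7.5% | 1.12 | 2.8% |
| 13.5 / 24.2 | 1.00 | 5% | 1.00 | 5% |

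Both errors vanish only if V_comb − V_clown = 585.64 − 182.25 = 403. That needs a combination SD of 24.2 if the clown SD is 13.5, or 31.4 if it is 24.2. Hydroxyzine would then have to lower the variance without clowns and raise it with them. Whenever the combination SD is no larger than the clown-only SD, the two errors run in the directions shown.

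**Interaction.** The contrast (combination − hydroxyzine) − (clown − control) has variance equal to the sum of the four group variances divided by 47. The pooled estimate is 4 × (mean of the four variances) / 47, the same number. With equal groups this test is protected whatever the SDs.

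**The case against.** Five points can be made for the plan.

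1. The SDs of two of the four groups are unknown, and each affected contrast involves one of them. This stands. The 45% figure belongs to one scenario, and a flat statement that the standard errors are wrong would go beyond the documents.

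2. The error term for the pairwise tests is not named. If they are two-sample tests, the distortion disappears in the base case, since each pair then shares one SD. This also stands, although the ANOVA error term is the usual reading of ANOVA followed by Bonferroni.

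3. The calculation uses one value per child, whereas the plan has four time-points, the first before any intervention. How far the planning SDs carry over to the repeated-measures error terms cannot be shown from the article. The percentages therefore indicate scale and do not predict the planned model exactly.

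4. Sizing and analysis are compatible for the comparison that sized the trial, because 47 per group rests on the same average variance that the pooled model uses. A reader might infer that the 90% power is wrong or that the test of additivity is invalid. The documents support neither: hydroxyzine v control has ratio 1.00 in the base case, and the 2×2 interaction is protected when groups are equal. Equal groups are not assured, since clown accompaniment depends on availability on the day.

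5. Variance handling is often left to the analysis plan. Here, however, the article does fix a method for the main outcome, and the ordinary form of that method does not fit its own planning figures. That goes beyond silence on a detail.

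**Conclusion.** The point holds conditionally. The article plans on a 3.2-fold variance ratio and then names a model that ordinarily assumes one variance.

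If the pairwise tests use the ANOVA error term and the clown groups share the SDs of their no-clown counterparts, clown v control is tested with a standard error about 19% too small. Combination v hydroxyzine is tested with one about 45% too large. With both unknown SDs between 13.5 and 24.2 and the combination SD no larger than the clown-only SD, the errors are 9–19% and 12–45%. Over a wider span (clown SD 13.5–24.2, combination SD 10–24.2) the ratios run from 0.79 to 1.00 and from 1.00 to 1.61.

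This is not a finding about the sample size. Away from the base case, over that wider span, the ratio for hydroxyzine v control lies between 0.83 and 1.12, depending on SDs that the article does not give. The change is worth making because it is nearly free. Confidence is medium, given the unknown SDs and the unstated error term.

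**What to change.** In Data analysis, replace the pooled-error ANOVA for the m-YPAS scores with a mixed model for the repeated scores in which residual variance may differ by group, or at least by hydroxyzine yes/no. Alternatively, keep the present framework and state that every between-group contrast uses Welch-type or heteroscedasticity-robust standard errors. In either case, name the error term that the Bonferroni comparisons use.

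The cost is a change of wording, a few lines of code and a few degrees of freedom. For hydroxyzine v control at 47 per group, moving from the pooled to the Welch test changes the calculated power from 90.3% to 89.1%. Trial conduct and sample size need not change.
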